**Figure 2. F2:**
[figure not shown]
Health Action Process Approach (HAPA)–based engagement messages for the Screening Results Page.

Once a participant initiates engagement by selecting one of the targeted Next Steps Content Pages, they may be randomized to see an engagement card embedded directly within the content page layout that targets 1 of the 4 HAPA behavioral determinants or MHA’s standard page design. These cards function as small user interface components that visually stand out but do not interrupt navigation. Cards are designed to provide a more visible but nondisruptive nudge to reinforce continued engagement. Each card will be embedded within the website interface and can be read without redirecting participants or requiring them to leave the page. HAPA-based engagement cards that will be delivered at the second decision point in the initial MRT are displayed in Figure 3.

**Figure 3. F3:**
[figure not shown]
Health Action Process Approach (HAPA)–based engagement cards for the Next Steps Content Pages.

#### Measures

##### Outcomes

Proximal engagement outcomes will be measured following each randomization. All engagement measures will be captured using server access logs, an objective measure of website browsing behavior, and bounded by 30 minutes of inactivity.

##### Primary Engagement Outcomes

At decision point 1 (Screening Results Page), the primary proximal outcome is initial engagement, which is defined as a binary indicator of whether a participant clicks to one of the targeted Next Steps Content Pages displayed on the Screening Results Page following randomization (yes or no). If a participant does not navigate to one of the targeted Next Steps Pages before leaving the MHA website or before the session ends due to 30 minutes of inactivity, then the outcome will be coded as “no.”

At decision point 2 (targeted Next Steps Content Pages), the primary proximal outcome is sustained engagement with MHA resources, which is defined as a binary indicator of whether a participant clicks to any additional substantive content page on the MHA website following randomization (yes or no). If a participant does not navigate to another content page before leaving the MHA website or before the session ends due to 30 minutes of inactivity, then the outcome will be coded as “no.”

##### Exploratory Engagement Outcomes

Exploratory proximal engagement outcomes are (1) total time (in seconds) spent on additional MHA content pages beyond the Screening Results Page and first targeted Next Steps Content Page; (2) total number of additional MHA content pages visited beyond the Screening Results Page and first targeted Next Steps Content Page; and (3) response, if available, to outcome questions displayed on Next Steps Content Page (eg, Was this helpful? Did this article help increase your knowledge and understanding of mental health? Did this article help you feel more confident in managing your mental health? and Did this article help you feel more hopeful about your mental health?).

For participants who click to another content page at decision point 2, specifically, sustained engagement with the targeted Next Steps Content Page will also be measured as total time (in seconds) spent on the page prior to navigating to the next page. For these participants, time on the targeted Next Steps Content Page can only be calculated when a subsequent navigation event occurs, as duration cannot be reliably computed when the Next Steps Content Page is the final page in a session.

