#### Secondary Aim Analysis

Secondary analyses will examine whether engagement strategies targeting distinct HAPA behavioral determinants differ in their relative effectiveness at increasing proximal engagement with targeted MHA content. Using the same weighted centered least squares estimation approach, models will compare the proximal effects of strategies targeting outcome expectancy (A*_t_*), risk perception (B*_t_*), self-efficacy (C*_t_*), and SGM-specific barriers to engagement (D*_t_*). These analyses will estimate marginal causal excursion effects for each strategy type. Additional analyses will examine whether variations of engagement strategies within the bank that target the same HAPA behavioral determinant differentially impact proximal engagement. These exploratory comparisons will be conducted by extending the primary regression models to include indicators for specific engagement strategy variations and estimating their relative causal excursion effects on proximal engagement outcomes. Exploratory analyses will also examine additional engagement outcomes (as described in the *Measures* section), including time spent on pages and the number of additional pages visited following exposure to intervention content.

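### Time on the Next Steps page exists only for participants who click onward, so comparing it between conditions conditions on the decision point 2 primary outcome

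*Protocol article*

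**What the plan says.** Under Primary Engagement Outcomes, the decision point 2 outcome is "a binary indicator of whether a participant clicks to any additional substantive content page on the MHA website following randomization (yes or no").

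Under Exploratory Engagement Outcomes, the first listed outcome is "total time (in seconds) spent on additional MHA content pages beyond the Screening Results Page and first targeted Next Steps Content Page". No restriction to clickers is attached to it. A further measure follows: "For participants who click to another content page at decision point 2, specifically, sustained engagement with the targeted Next Steps Content Page will also be" (the sentence goes on to define this in seconds on that page). The reason given is that "duration cannot be reliably computed when the Next Steps Content Page is the final page in a session".

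The Outcomes section gives the data source: "All engagement measures will be captured using server access logs, an objective measure of website browsing behavior, and bounded by 30 minutes of inactivity". The Secondary Aim Analysis says that "Exploratory analyses will also examine additional engagement outcomes" from the Measures section, "including time spent on pages and the number of additional pages visited following exposure to intervention content".

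The article explains why the page time cannot be computed for non-clickers. Neither that section nor the limitations in the Discussion says what the restriction does to a comparison between conditions.

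**The concern.** The condition for having a page time is the same event as a primary outcome of yes at decision point 2. The cards are there to make that event more frequent. If they succeed, the strategy clickers include people who would have left under control, while the control clickers do not include their counterparts. The two groups then differ in who they contain, whether or not a card changes how long anyone reads.

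This is not the same as restricting the decision point 2 analysis to participants who reached a Next Steps page. That restriction is settled before the second randomization, which is independent of the first. Clicking onward comes after it.

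At stake is a misleading exploratory result: a card that draws in hesitant visitors could seem to shorten reading, or to lengthen it, when no one's reading time changed.

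**Working it through.** **Inputs from the Sample Size section.** Control success probability 0.30; risk ratio 1.20; probability of any strategy 0.80; average availability 0.70 over two decision points, with full availability at the first; 80% power; two-sided alpha 0.05; stated minimum of 2300 participants.

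**The plan's own figure.** The closed-form size for a binary proximal outcome with a constant effect is

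n = (1.960 + 0.842)² × [(1 − p)/RR + p − p0] / [T × τ × p(1 − p) × p0 × (ln RR)²]

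with p = 0.80, τ = 0.70, T = 2, p0 = 0.30 and RR = 1.20. The bracket is 0.20/1.20 + 0.80 − 0.30 = 0.667. The result is 2342, within 2% of 2300, and power at 2300 is 79.3%. The stated figure reproduces, so the same inputs are used below.

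**Who has a page time.**
- Availability at decision point 2: 2 × 0.70 − 1.00 = 0.40.
- Randomized there: 2300 × 0.40 = 920, of whom 184 control and 736 strategy.
- Clickers: 184 × 0.30 ≈ 55 control; 736 × 0.36 ≈ 265 strategy.
- Page time is undefined for 70% of control and 64% of strategy participants.

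**Size of the selection.** If strategies only add clickers, the added share of strategy clickers is (0.36 − 0.30)/0.36 = 1/6. Let added clickers stay r times as long as the others, and let no one else's time change. The apparent strategy/control ratio of mean time is 5/6 + r/6:

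| r (assumed) | apparent ratio |
|---|---|
| 0.25 | 0.875 |
| 0.5 | 0.917 |
| 1 | 1.00 |
| 2 | 1.17 |

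**Effect on a test.** Simulation of a nominal 5% test among clickers, with log-normal times (assumed SD 0.8 on the log scale) and no effect on anyone who would click either way:

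| enrolled | r = 1 | r = 0.5 | r = 0.25 |
|---|---|---|---|
| 2300 | 4.6% | 16% | 46% |
| 10,000 (assumed) | 5% | 52% | 97% |

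A larger sample makes the false signal more likely. The Results section reports 3878 enrolled by April 13, 2026.

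**Total time on additional pages.** With non-clickers coded 0, everyone randomized at decision point 2 has a value. Assume a mean of two additional pages per clicker, 60 s per page, and no recorded duration for the last page. The expected true difference at risk ratio 1.20 is 0.06 × 2 × 60 = 7.2 s, and the recorded one is 0.06 × 1 × 60 = 3.6 s. Simulation gave 7.3 s and 3.8 s. With no effect the simulated recorded difference was about zero (0.16 s; rejection 6.6%, slightly above nominal because the data are skewed and the control group is small). The measure is shortened, but the comparison stays randomized.

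**The case against.** The measure is exploratory, the article openly gives the technical reason for the restriction, and it names no causal excursion estimand for page time among clickers. All of that is correct, and it limits the weight of the point. But the restricted population is fixed in the article itself, page time is introduced among the proximal outcomes measured after randomization, and nothing confines it to description. A comparison between conditions is the natural reading.

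The direction and size of the distortion rest on assumed reading times. That also stands: if added clickers read as long as the others, there is no distortion. The documents give no reading times, so only a range can be shown.

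A reader might infer that total time on additional pages is equally compromised because its last page also lacks a duration. The text does not support this. That outcome is not limited to clickers, and a participant with no additional page has a natural value of zero. It would become a selected comparison only if sessions with an unmeasured last page were dropped, and the article does not say so; its complete-case rule is written for the primary analysis. Nor is the last content page always lost, since a later logged request could close it. It would also be wrong to count non-clickers as unmeasured. If 60% of strategy clickers view one extra page (assumed), 64% of strategy participants have a true zero, 0.36 × 0.4 = 14.4% have a partly recorded time, and 0.36 × 0.6 = 21.6% are recorded as zero despite visiting a page.

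**Conclusion.** The point holds for time on the Next Steps page. Compared between conditions, it is conditional on a post-randomization outcome that the cards aim to change. Under the plan's 30% and 36%, one sixth of strategy clickers would be added clickers, assuming strategies only add clickers. The apparent time ratio could then lie between about 0.875 and 1.17 with no effect on anyone else's time, assuming added clickers stay 0.25 to 2.0 times as long.

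For total time on additional pages the defect is under-measurement only, given zero coding for non-clickers.

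A reader might also infer that a biased page time will steer which strategies are kept between iterations. The section on refinements refers to prespecified decision rules and strategy performance but names no time outcome, so that consequence is not established. The primary outcomes, primary analysis and sample size are untouched.

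**What to change.** State that time on the Next Steps page among clickers will be reported descriptively by condition, with no causal excursion effect estimated from it. Base any causal contrast on time on an outcome defined for everyone randomized at decision point 2, for example total time on additional pages coded 0 if there were none. When interpreting that total, say that it generally omits the last page viewed and so understates time, and that it reflects clicking onward as well as reading.

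The change needs only logs already captured and does not alter randomization, the primary outcomes or the sample size. The cost is that there is no causal estimate for time on the Next Steps page itself, and the time spent on the last page stays unmeasured.

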##### Moderators and Covariates

All moderator and covariate measures will either be derived from server access logs or collected through MHA’s standard screening and optional postscreening survey.

##### Time-Varying Moderators

The number and type of MHA pages visited prior to a decision point will be treated as a time-varying moderator, as the value may differ depending on how much content a participant has accessed earlier in the session. These indicators capture the participant’s current engagement state at the moment the engagement strategy is delivered and allow examination of whether the effect of the strategy differs depending on earlier browsing behavior.

##### Time-Invariant Moderators

Sexual orientation, gender identity, age, baseline symptom severity (ie, PHQ-9 score), and participants’ stated postscreening intentions for using MHA (eg, reading articles, try a free self-help tool, and do nothing) will be treated as time-invariant moderators.

##### Covariates

Race or ethnicity and income will be treated as control variables.

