### Objective

The overall objective of this study is to test theory-based engagement strategies within the existing web infrastructure of a real-world DMH platform. Using a series of MRTs, engagement strategies designed to target HAPA’s immediate behavioral determinants will be delivered at 2 key decision points within the flow of MHA’s Online Screening Program to examine whether and which engagement strategies increase SGM visitors’ proximal engagement with MHA resources.

The primary aim is to evaluate whether delivering (vs not delivering) HAPA-based engagement strategies increases naturalistic engagement with MHA resources. Within this primary aim, we will also explore whether (1) the effectiveness of delivering (vs not delivering) engagement strategies differs across the 2 decision points and (2) the effects of delivering (vs not delivering) engagement strategies are moderated by time-invariant and time-varying factors.

The secondary aim is to examine whether engagement strategies targeting distinct HAPA behavioral determinants differ in their relative effectiveness in increasing naturalistic engagement with MHA resources. Within this secondary aim, we will also explore whether specific engagement strategy variations targeting the same HAPA behavioral determinant differentially impact proximal engagement.

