### Data Analysis Plan

#### Primary Aim Analysis

Analyses will estimate the marginal causal excursion effects of delivering engagement strategies on proximal engagement with MHA content. Data will be analyzed using the weighted centered least squares estimator, which provides consistent estimates of causal excursion effects when including time-varying factors that may be influenced by prior intervention exposure [36,45,48]. Analyses will examine whether, on average, across decision points, engagement strategies (A*_t_*-D*_t_*) increase proximal engagement with targeted MHA content relative to the control (Z*_t_*). A log-linear model will be used, as the primary proximal outcome is binary (engaged vs not engaged with targeted content). For the primary analysis, all HAPA-based engagement strategies (A*_t_*-D*_t_*) will be pooled so that the estimated marginal causal excursion effect represents the average effect of delivering any engagement strategy compared with the control (Z*_t_*). Effects will be expressed as the log of a risk ratio (ie, the probability of engagement when an engagement strategy is delivered relative to the probability of engagement when the control is delivered at a decision point). To examine whether intervention effects differ across the 2 decision points, models will include an interaction between intervention assignment and a decision point indicator. Baseline characteristics (eg, sexual orientation, gender identity, age, baseline PHQ-9 score, and intentions for using MHA) and time-varying contextual factors (eg, number and type of pages visited prior to a decision point) will also be examined as potential moderators of proximal intervention effects by including interaction terms in the log-linear model. Models will control for race or ethnicity and income.

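### The pooled primary effect is not stated to be adjusted for age, PHQ-9 score or stated intention, although all are collected before randomization; adding them could gain precision at almost no cost

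*Protocol article*

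**What the plan says.** The control set is named twice in the protocol article. Covariates: "Race or ethnicity and income will be treated as control variables". Primary Aim Analysis: "Models will control for race or ethnicity and income". No other control variable is named.

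Time-Invariant Moderators gives age, PHQ-9 score and "participants’ stated postscreening intentions for using MHA (eg, reading articles, try a free self-help tool, and do nothing" a moderator role, alongside sexual orientation and gender identity. Primary Aim Analysis says that these "will also be examined as potential moderators of proximal intervention effects by including interaction terms in the log-linear model".

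The primary target is a single pooled contrast, in which "the estimated marginal causal excursion effect represents the average effect of delivering any engagement strategy compared with the control". Decision point enters the same section through a different question: "models will include an interaction between intervention assignment and a decision point indicator". The Objective section presents that question as exploratory: "Within this primary aim, we will also explore whether (1) the effectiveness of delivering (vs not delivering) engagement strategies differs across the 2 decision points". The article does not say whether the single-effect pooled model also carries a decision point main effect.

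**The concern.** In a randomized comparison, the useful control variables are those that predict the outcome. A visitor who has just said that they intend to read articles, or to do nothing, may well differ in the chance of clicking. Symptom severity and age may also matter. The plan holds these variables but uses them only to ask whether the effect varies, not to sharpen the average effect.

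Completeness points the same way. Age is an eligibility item and the PHQ-9 must be completed to enter (Eligibility Criteria), so both should be complete. Missing Data warns that other survey items may be missing because they are optional. That covers race or ethnicity and income, the two controls chosen, and also stated intention.

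The pooled effect also averages two different outcomes (Primary Engagement Outcomes): a click to a targeted page at decision point 1, and a click to any further content page at decision point 2. The second is measured only in those who reached a Next Steps page. If the two baseline rates differ, a decision point term removes some residual variance.

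At stake is precision. Only 20% of assignments are control. The secondary models use the same estimator, and the variation comparisons extend the primary models, so the control set may carry over to comparisons that the Sample Size section says need a larger sample.

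**Working it through.** **1. Reproduce the planned sample size without covariates.** Inputs from Sample Size: 80% power, two-sided α 0.05, probability of any strategy p = 0.80, availability 0.70 over 2 decision points (2 × 0.70 = 1.4 randomizations per participant), control success μ = 0.30, risk ratio 1.20.

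- V = (1/RR − μ)/(pμ) + (1 − μ)/((1 − p)μ) = (0.8333 − 0.30)/0.24 + 0.70/0.06 = 2.222 + 11.667 = 13.889
- n = (1.960 + 0.842)² × V / (1.4 × (ln 1.20)²) = 7.849 × 13.889 / 0.04654 = 2342

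The F reference distribution gives 2345. The stated 2300 is within 2% of both, so the plan takes no credit for covariates.

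**2. Effect on the estimand.** The estimator multiplies a residual, which contains the fitted control part, by (assignment − 0.80). Control terms are fixed before assignment, and Sequence Generation makes the probabilities constant and independent of participant characteristics. Their product with (assignment − 0.80) therefore has mean zero. Adding such terms changes the variance but not the target.

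**3. Size of the gain.** Let R² be the share of outcome variance explained by the added variables. Then V falls by R² × (1 − μ)/μ × (1/p + 1/(1 − p)) = R² × 2.333 × 6.25 = 14.58 × R². The documents give no R², so the values below are assumptions.

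| Assumed R² | Required n | Change | Power at 2300 |
|---|---|---|---|
| 0 | 2342 | 0 | 79.3% |
| 0.02 | 2293 | −2.1% | 80.1% |
| 0.05 | 2219 | −5.2% | 81.4% |
| 0.10 | 2096 | −10.5% | 83.5% |
| 0.15 | 1974 | −15.7% | 85.6% |

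For scale: three equal intention groups with click rates 0.20/0.30/0.40 give R² 0.032, rates 0.15/0.30/0.45 give 0.071, and rates 0.10/0.30/0.50 give 0.127.

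**4. Decision point alone.** With relative weights 1 and 0.4 (0.40 is the decision point 2 availability implied by an average of 0.70), R² is 0 under the plan's constant 0.30. If the decision point 2 control rate were 0.20, 0.40, 0.50 or 0.60, R² would be 0.010, 0.009, 0.036 or 0.078.

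**5. Simulation check.** The log-linear estimator was run with session-clustered standard errors: n = 2300, RR 1.20, 600 replicates per setting, decision point 2 reached only after a click at decision point 1. The baseline model has a two-level non-prognostic control. Entries are mean squared SE relative to that model.

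| Decision point 2 control rate | Intention rates (ratio) | + decision point | + decision point and intention |
|---|---|---|---|
| 0.30 | no effect | 1.000 | 1.000 |
| 0.30 | 0.15/0.30/0.45 | 0.997 | 0.927 |
| 0.50 | no effect | 0.965 | 0.965 |
| 0.45 | 0.20/0.30/0.40 | 0.970 | 0.930 |
| 0.45 | 0.15/0.30/0.45 | 0.956 | 0.873 |

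In every setting the mean estimate agreed across models to within 0.001 and lay between 0.180 and 0.188 (true value ln 1.20 = 0.182). The second row's 7.3% reduction matches the 7.5% that the formula gives at R² 0.071.

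**6. Where precision is tighter.** One determinant against control (0.20 versus 0.20, RR 1.20, no multiplicity correction): V = 0.5333/0.06 + 0.70/0.06 = 20.556, so n = 7.849 × 20.556 / 0.04654 ≈ 3470. An assumed R² of 0.10 lowers V by 0.10 × 2.333 × (5 + 5) = 2.333, or about 11%.

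**The case against.** The strongest reply is that this is a preference and not a flaw. The primary comparison meets its target without adjustment. Enrollment stood at 3878 about a month after the initial trial opened. If all of those belong to the first iteration (the article gives no boundary), unadjusted power is 95.0%, and an assumed R² of 0.10 raises it only to 96.8%. That stands, and it limits what the point is worth for the primary comparison.

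Prognostic value is also undocumented. Preliminary Work names outcome expectancies, perceived risk, self-efficacy and barriers as among the strongest determinants, not age or PHQ-9 score. The Introduction describes a gap between stated intention and behavior, so intention may predict weakly. That stands too: the gain may be zero. Intention is as optional as race or ethnicity and income, so optionality cannot be held against those two alone.

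Three stronger readings are tempting, and the documents do not support them:

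- *The plan leaves decision point out.* Primary Aim Analysis includes a decision point indicator through the interaction. Only its place in the pooled single-effect model is unstated.
- *The plan ignores age, PHQ-9 score and intention.* They are in the log-linear models as moderators. What is not stated is that the pooled effect is adjusted for them.
- *The primary comparison is short of precision, or biased.* The planned number reproduces without covariates, and the estimates do not shift when they are added.

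It may also be said that covariate detail belongs in an analysis plan. That does not fully answer the point, because the article itself fixes the control set, twice.

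**Conclusion.** The point holds as a low-cost gain in efficiency. The plan names race or ethnicity and income as its only controls and gives age, PHQ-9 score and stated intention a moderator role only. Using them as controls as well leaves the pooled effect unchanged and cannot bias it, given fixed assignment probabilities.

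The size cannot be taken from the documents. It is zero if the variables are not prognostic, and about 2% to 16% fewer participants for an assumed R² of 0.02 to 0.15. Under the plan's own constant 0.30, the decision point term adds nothing; it helps only if the two baseline rates differ. Because the primary comparison is adequately sized without adjustment, the benefit falls mainly on smaller effects, later iterations and the determinant-level comparisons, which inform what is kept from one iteration to the next.

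**What to change.** State in Covariates and Primary Aim Analysis that the control part of the pooled primary model, and of the secondary models that use or extend it, includes:

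- age and PHQ-9 score, both expected to be complete;
- stated intention, with a 'not reported' category so that no participant is lost;
- the decision point main effect, already implied in the interaction model.

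Race or ethnicity and income can stay, with the same handling of non-response. Keep the treatment part as one pooled term, so that the estimand does not change, and leave the moderator analyses as they are.

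Fix this before outcomes are analyzed, since covariates added afterwards would look data-driven. The cost is one sentence and a few model terms. No new data are needed, and the sample size does not change.
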